After receiving the completed consent forms and questionnaire, the study team will provide practices with patient identifiable data (names, date of birth and address) of patients who have been recruited to this nested assessment of agreement. Electronic primary care records will then be accessed by the practice team to identify the unique Vfrac reference number for each patient recruited to this nested study and this will be shared with the study team to assess the agreement between face-to-face completion by a healthcare professional and self-completion by the patient.

### Quantitative data analysis

Outputs (high risk versus low risk of VVF) of the self-completion Vfrac questionnaire will be compared with those from the face-to-face Vfrac completed at the general practice during WP1, and agreement assessed using Cohen’s kappa. Responses to the satisfaction and ease of use questions will if necessary be used to modify the tool for future use.

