**Nested qualitative assessment of acceptability**	**Outputs**
Outcome measures from participants recruited at intervention practices 2.1 Understanding of acceptability to healthcare professionals and patients 2.2 Identification of factors that impact on implementation, including barriers and facilitators to delivery	1. Results will form the basis of recommendations to modify Vfrac and improve delivery in any future trials

**Nested assessment of agreement between the use of Vfrac within general practices and self-completion at home**	**Outputs**
Outcome measures from participants recruited from intervention practices 3.1 Outputs of self-completion Vfrac 3.2 Satisfaction and ease of the use of self-completion questionnaire 3.3 Participants views of whether they preferred face-to-face assessment in primary care or self-completion at home 3.4 Assessment of agreement between outputs of the self-completed Vfrac and face-to-face Vfrac using Cohen’s kappa	1. Decision as to whether Vfrac can be carried out as a self-completion assessment or whether it needs to be delivered face-to-face for any future trial 2. Summary statistics for proportions of participants satisfied with process, interpersonal and technical attributes will be calculated 3. Recommendations in free-text fields of the satisfaction and ease of use questions will be used to modify the (future) tool if necessary

A clinical update on osteoporosis will be offered to all. Three practices will then be assigned to the intervention arm and three to the control by purposeful selection to ensure there are both large and small practices in both groups that have varying levels of deprivation. The control practices will use standard clinical processes for older women consulting with back pain. Those in the intervention arm will be trained in the use of Vfrac and will have it made accessible from their IT systems (through provision of a URL via pop-ups on typing relevant words such as back pain). The use of the Vfrac tool will be encouraged within their clinical pathways for management of older women (over 65 years of age) who consult with back pain. The use of the tool in a manner that is in accordance with each practice’s service delivery model will be facilitated by the research team in discussion with the clinical team. As the use of Vfrac poses only minimal/no risk, the use of a waiver of consent by individual patients for this cluster-level intervention is appropriate [15].

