### Data collection

Data will be collected from the online Vfrac tool. When healthcare professionals enter data into the tool after clicking on the URL, inbuilt analytics will be used to record the Vfrac score, length of time taken and completeness of data collection. For each individual patient, once the data have been submitted, the Vfrac result (low or high risk of VFF) and recommendations will be available as a ‘copy and paste’, along with a unique Vfrac code (watermark). This will then be recorded in the individual patient’s medical records. Each practice will have their own URL allowing secure access to the online Vfrac tool, and also to allow analysis of differences in data collection across practices. No patient identifiable data will be recorded by the online Vfrac tool, the data stored will include the answers to each question for every entry per practice, the resulting Vfrac score, date submitted and unique Vfrac reference code generated per record. There will be no ability to link back any data to individual patients, only to practices. The Vfrac result and recommendation for each individual patient will have been copied and pasted into the medical records at the time of the consultation and will be captured during the electronic download from the general practices every three months using the watermark.

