### WP3: nested assessment of agreement between the use of Vfrac within general practices and self-completion at home

Based on assessment of agreement using Cohen’s kappa, and assuming approximately 30% of Vfrac outputs will be classified as high risk, for a sample size of 60 (20 from each intervention practice), the margins of error from 95% confidence intervals around estimates of kappa in the range 0.8–0.6 (the definition of substantial agreement) would be from 0.16 to 0.22. This level of precision is deemed sufficient for these purposes.

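### WP3 names only Cohen's kappa for agreement, so a one-way shift between home and practice completion could pass as substantial agreement

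*Protocol article*

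**What the plan says.** The WP3 section on quantitative data analysis sets out the comparison: "Outputs (high risk versus low risk of VVF) of the self-completion Vfrac questionnaire will be compared with those from the face-to-face Vfrac", with "agreement assessed using Cohen’s kappa". The abstract and item 3.4 of Table 2 name the same statistic and no other for agreement. Table 2 lists the resulting output as "Decision as to whether Vfrac can be carried out as a self-completion assessment" or must be delivered face-to-face in a future trial.

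The WP3 sample size section takes 60 women, 20 from each of three intervention practices, "assuming approximately 30% of Vfrac outputs will be classified as high risk". It quotes "margins of error from 95% confidence intervals around estimates of kappa in the range 0.8–0.6", which it equates with substantial agreement, and says these margins "would be from 0.16 to 0.22. This level of precision is deemed sufficient for these purposes".

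Three other statements bear on the point:

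- The Background says a low-risk output means a spinal X-ray is not recommended and a high-risk output means it is.
- The WP3 section voices concern that women with vertebral fractures may struggle to measure their own wall-to-tragus distance, and obtains radiology data for that reason.
- Under WP1 data collection, "inbuilt analytics will be used to record the Vfrac score" for the practice version, and the individual answers are stored. The unique code later links each practice record to the woman's paper questionnaire.

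**The concern.** Kappa on a 2×2 table depends mainly on how many pairs disagree and only weakly on which off-diagonal cell they fall in. Here the two cells have different consequences. One holds women for whom the practice version recommends an X-ray and the home version does not. The other holds the reverse. Random disagreement leaves the number of X-ray recommendations about the same; a systematic shift changes it.

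A systematic shift is plausible on the protocol's own account, because the home version relies on a self-measurement that the authors expect some women to find hard. If the delivery decision is read off kappa, a future trial could adopt a mode that recommends materially fewer or more X-rays than the practice version, on the strength of a value in the range called substantial.

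**Working it through.** **Inputs.** From the WP3 sample size section: n = 60, about 30% high risk (18 of 60), 95% confidence, kappa 0.6 to 0.8. Assumed here: the same 30% in both modes for the precision check, and no clustering by practice.

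**Step 1: the plan's own margins.** Chance agreement is pe = 0.3² + 0.7² = 0.58, and observed agreement is po = pe + kappa × (1 − pe). The simple half-width is 1.96 × √(po(1 − po)/n)/(1 − pe).

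- Kappa 0.8: po = 0.916; 1.96 × √(0.916 × 0.084/60)/0.42 = 0.167.
- Kappa 0.6: po = 0.832; 1.96 × √(0.832 × 0.168/60)/0.42 = 0.225.

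The full large-sample (Fleiss–Cohen–Everitt) standard error gives 0.167 and 0.222. The stated 0.16 to 0.22 is therefore essentially reproduced. The lower figure would round to 0.17 at 30% prevalence and is 0.160 at 35%.

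**Step 2: direction.** Rows are face-to-face and columns are self-completion, so cells read high/high, high/low, low/high, low/low. Kappa = (po − pe)/(1 − pe). In each eight-pair table po = 52/60 = 0.867.

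| Cells | pe | Kappa | High-risk outputs, practice to home |
|---|---|---|---|
| 14, 4, 4, 38 | (18×18 + 42×42)/3600 = 0.580 | 0.68 | 18 to 18 |
| 10, 8, 0, 42 | (18×10 + 42×50)/3600 = 0.633 | 0.64 | 18 to 10 (8/18 = 44% fewer) |
| 18, 0, 8, 34 | (18×26 + 42×34)/3600 = 0.527 | 0.72 | 18 to 26 (44% more) |

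Six changes, all high to low (12, 6, 0, 42), give po = 0.90, pe = 0.62 and kappa 0.74, with 6/18 = 33% fewer X-ray recommendations. Six balanced changes give 0.76.

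**Step 3: what a directional summary shows on the same tables.** The paired difference is (b − c)/n, with standard error √(b + c − (b − c)²/n)/n, where b and c are the high/low and low/high counts.

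- Split 4/4: difference 0; 1.96 × √8/60 = 0.092; 95% CI −9.2 to 9.2 percentage points; exact McNemar p = 1.0.
- Split 8/0: difference 8/60 = 13.3 points; 1.96 × √(8 − 64/60)/60 = 0.086; 95% CI 4.7 to 21.9 points; exact McNemar p = 2 × 0.5⁸ = 0.008.

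Kappa differs by only 0.05 between these tables (0.683 against 0.636), well within its margin of error. The paired difference separates them.

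**Step 4: what the stated precision supports.** Using the Step 1 standard error, the 95% CI is 0.63 to 0.97 at an estimate of 0.8, 0.50 to 0.90 at 0.7, and 0.38 to 0.82 at 0.6. The lower limit reaches 0.6 at an estimate of about 0.78. In 20,000 simulated studies per value, the lower limit reached 0.6 in 5%, 23%, 62% and 96% of studies at true kappa 0.6, 0.7, 0.8 and 0.9.

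**The case against.** The strongest reply is that this is a feasibility study with an openly stated precision target whose arithmetic holds. The 2×2 table has to be built to compute kappa, so cells of 8 and 0 would be seen. Paired differences and Bland–Altman plots are the sort of detail left to an analysis plan, which is not shown. Kappa is also not the only WP3 evidence: Table 2 lists the self-completed outputs, satisfaction and ease of use, and preferred mode, and radiology data are obtained because of the measurement worry. The decision concerns delivery in a future trial, not adoption in care.

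Much of this stands. A reader might infer any of the following, and the documents do not support them:

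- **That 60 pairs cannot separate moderate from almost perfect agreement.** An estimate of 0.8 has a 95% CI of 0.63 to 0.97, which excludes values below 0.6.
- **That the interval must fit inside 0.6 to 0.8.** The protocol gives that as a range of estimates for planning and sets no such requirement.
- **That self-completion would cut X-ray recommendations.** The protocol gives a reason for error but no direction; recommendations could equally rise.
- **That WP3 as a whole rests on kappa.** It is the only agreement statistic named, not the only outcome.

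What the reply does not answer is that the article fixes a method, names it in three places and attaches a decision to it. That method does not measure the kind of disagreement the protocol itself has cause to worry about. Satisfaction and preference do not address it either, and no use of the radiology data in the agreement analysis is described.

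**Conclusion.** The point holds as an improvement to the named analysis, not as an error in the sample size. With 18 of 60 women high risk face-to-face, a one-way loss of 33% to 44% of X-ray recommendations still gives kappa 0.74 to 0.64, and a 44% gain gives 0.72. The protocol would call all of these substantial. The tables are illustrations, not predictions. They assume 30% high risk in the practice and treat face-to-face completion as the comparator, not as the truth about fracture.

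On precision, only a qualification is needed. The margins are sound, but for estimates from 0.6 up to about 0.78 the interval extends below 0.6. That cut-off assumes equal 30% margins and no clustering. At 20% high risk the margins at kappa 0.8 and 0.6 would be 0.19 and 0.26; at 40%, 0.155 and 0.21.

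**What to change.** Keep 60 pairs and report kappa with its 95% CI. In the WP3 quantitative data analysis section, add:

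1. the 2×2 table of face-to-face against self-completed output;
2. the paired difference in proportion high risk, with 95% CI and exact McNemar test;
3. the proportion of face-to-face high-risk women who are also high risk on self-completion, with its CI;
4. a Bland–Altman comparison of the Vfrac score and of wall-to-tragus distance, where both can be derived as continuous values in both modes. The protocol records a score for the online version; for the paper version it would have to be calculated from the answers.

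State that the delivery-mode decision will rest on the direction of disagreement as well as on kappa. In the WP3 sample size section, qualify the claim of sufficient precision: with 60 pairs the 95% CI excludes kappa below 0.6 only when the estimate is about 0.78 or higher, and an estimate of 0.70 has a CI of 0.50 to 0.90.

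This needs no extra patients and no new data for items 1 to 3. The costs are slightly more analysis and a less favourable precision statement. Item 3 will be imprecise because it rests on about 18 women: 10/18 = 56%, with a simple half-width of 1.96 × √(0.556 × 0.444/18) = 23 percentage points. It should be read with item 2, not alone.

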To address this, we have developed the Vfrac clinical decision tool to help primary healthcare practitioners decide if an older woman with back pain is at high risk of a VFF and therefore requires a spinal radiograph to confirm the diagnosis. Vfrac is targeted for use during consultations between a healthcare professional and an older woman consulting with back pain. Vfrac is the only evidence-based decision tool developed from research involving women with and without VFFs including qualitative[8], cross-sectional [9–11] and case–control studies [12]. The Vfrac tool comprises 15 questions based on self-reported data and a physical examination and takes approximately 5 minutes to perform. It has been made available on a web-based online interface to make it accessible for use across different IT systems in primary care in the UK. Use of the pre-determined cutoff [13] produces the output (“low risk—spinal X-ray is not recommended”—or “high risk—spinal X-ray is recommended as may have a vertebral fracture”). As previously published [14], the Vfrac clinical tool has an area under the curve (AUC) of 0.802 (95% CI 0.764–0.840). Statistical modelling shows no evidence of over/underfitting; optimism in the estimate of the AUC was 0.019 estimated using 500 bootstrapped samples; and multiple imputation to account for the missing data produced results that were similar to our final model and provides internal validation. A pre-trial economic evaluation, also published [14], calculates the incremental cost-effectiveness ratio (ICER) for Vfrac compared to standard care is £17,000 per QALY and Vfrac has the potential to be cost-effective but a definitive trial is warranted.

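### Cohen's kappa, the only agreement statistic named for WP3, does not show the direction of disagreement: at the planned size, losing 7 of 18 clinic-high women at home and losing none both give a kappa of about 0.7

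*Protocol article*

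**What the plan says.** The WP3 section on quantitative data analysis states that "Outputs (high risk versus low risk of VVF) of the self-completion Vfrac questionnaire will be compared with those from the face-to-face Vfrac" done during WP1, "and agreement assessed using Cohen’s kappa". The abstract and Table 2 (outcome 3.4) name the same statistic, and the article names no other measure of agreement. The WP3 sample size rests on the precision of kappa. It takes 60 women, "assuming approximately 30% of Vfrac outputs will be classified as high risk", and finds that the 95% margins of error for kappa between 0.8 and 0.6, a range it labels substantial agreement, "would be from 0.16 to 0.22".

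Table 2 gives the purpose of WP3 as a "Decision as to whether Vfrac can be carried out as a self-completion assessment or whether it needs to be delivered face-to-face" in a future trial. Beside kappa it lists the self-completion outputs (3.1), satisfaction and ease of use (3.2) and preference for setting (3.3). The Background explains what the two outputs mean: low risk carries the message "spinal X-ray is not recommended", and high risk the opposite.

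**The concern.** Kappa for two binary outputs is symmetric. Exchanging the two discordant cells of the 2x2 table leaves it unchanged, so it cannot tell a downward shift at home from an upward one. The two shifts have different consequences. A downward shift withholds the X-ray recommendation from women to whom the clinic assessment gave it. An upward shift adds radiographs, whose radiation dose the Discussion counts as a drawback.

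The WP3 section also gives a reason to expect systematic rather than random disagreement, because women with vertebral fractures may find the home wall-to-tragus measurement difficult. It does not say which way this would move the result, so the direction has to be measured. If the choice between home and face-to-face delivery were informed mainly by a kappa of about 0.7, two home forms that behave very differently would look alike.

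**Working it through.** **Inputs.** From the WP3 sample-size section: n = 60 pairs, about 30% high risk, kappa 0.6 to 0.8. I apply the 30% to the clinic outputs, which gives 18 clinic-high and 42 clinic-low women.

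**The article's own figure.** With both methods at 30% high risk, chance agreement is pe = 0.3² + 0.7² = 0.58, and observed agreement is po = kappa × (1 − pe) + pe.
- Kappa 0.8: po = 0.916. Simple margin = 1.96 × √(0.916 × 0.084 / 60) / 0.42 = 0.167. The Fleiss-Cohen-Everitt standard error, with disagreement split evenly, also gives 0.167.
- Kappa 0.6: po = 0.832. Simple margin 0.225; Fleiss-Cohen-Everitt 0.222.

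The stated 0.16 to 0.22 is therefore reproduced, apart from truncation of the lower figure.

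**Kappa under three patterns of disagreement.** Kappa = (po − pe) / (1 − pe), with pe taken from the margins of each table.
- 4 down, 4 up: po = 52/60 = 0.867; pe = (18×18 + 42×42)/3600 = 0.580; kappa = 0.683.
- 0 down, 8 up: po = 52/60 = 0.867; pe = (18×26 + 42×34)/3600 = 0.527; kappa = 0.718.
- 7 down, 0 up: po = 53/60 = 0.883; pe = (18×11 + 42×49)/3600 = 0.627; kappa = 0.6875.

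An exact tie also exists. With 0 down and 9 up, po = 0.850, pe = (18×27 + 42×33)/3600 = 0.520 and kappa = 0.6875.

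**What directional measures show for the same tables.** The paired difference is (up − down)/60, with a large-sample interval of ±1.96 × √[(up + down) − (up − down)²/60] / 60.

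| Pattern | Kappa (95% CI) | Clinic-high still high | Clinic-low still low | High at home | Paired difference, points (95% CI) | Exact McNemar p |
|---|---|---|---|---|---|---|
| 4 down, 4 up | 0.68 (0.48–0.89) | 14/18 = 78% | 38/42 = 90% | 18/60 = 30% | 0 (−9 to +9) | 1.0 |
| 0 down, 8 up | 0.72 (0.54–0.89) | 18/18 = 100% | 34/42 = 81% | 26/60 = 43% | +13 (+5 to +22) | 0.008 |
| 7 down, 0 up | 0.69 (0.48–0.89) | 11/18 = 61% | 42/42 = 100% | 11/60 = 18% | −12 (−20 to −4) | 0.016 |

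The kappas lie within 0.04 of one another and their intervals almost coincide. The other columns separate the three forms.

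**Sensitivity.** Losing 8 of 18 (44%) with none gained still gives kappa 0.636; losing 9 gives 0.583 and leaves the 0.6 to 0.8 range. If 20% to 50% of women are clinic-high, losing 37% to 42% of them (5/12, 6/15, 8/21, 10/24, 11/30) gives kappa 0.63 to 0.69. The result does not depend on exactly 30%.

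**Precision of the added quantity.** Exact 95% intervals: 11/18 gives 36% to 83%, and 18/18 gives 81% to 100%.

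**The case against.** Kappa is a standard choice for two binary outputs, and the article does not say that nothing else will be reported. Outcome 3.1 lists the self-completion outputs in their own right. Each recruited woman's home form is to be linked to her clinic result, so the 2x2 table will exist, and an analysis plan that is not shown may use it. The one-way tables above are extreme. With about 18 clinic-high women a test has little power: 5 lost and none gained gives an exact McNemar p of 0.0625.

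Much of this stands. Outcome 3.1 could show the overall proportion high risk at home, and the small numbers argue against a pass/fail test. But no stated analysis compares that proportion with the clinic proportion in the same women, or gives agreement separately for clinic-high and clinic-low women. A matching overall proportion would also not show how many women moved each way. The article itself chose kappa and judged its precision sufficient, so this is more than a detail left to another document.

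A reader might infer three stronger things that the documents do not support.
- That kappa alone decides. Table 2 sets outcomes 3.1 to 3.3 beside it and ties the decision to no single statistic.
- That a kappa of 0.6 to 0.8 is a pass mark. The range is used only to illustrate precision, and the stop/go criteria in the Discussion contain no kappa threshold.
- That 7 women lost means 7 fractures missed. The clinic output is itself imperfect (AUC 0.802, with two-thirds of women with a single fracture identified), so some downward moves could be corrections.

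**Conclusion.** The concern holds as a limitation of the stated agreement analysis. Kappa is valid and its quoted margins are sound, but it carries no information on direction. At the article's own sample size and prevalence, a kappa near 0.7 is compatible with 39% (7/18) of clinic-high women being reclassified as low at home and with none being so. This rests on 60 complete pairs and about 30% clinic-high. It uses one-directional tables to show what kappa can conceal, not to predict what will happen. Losses are measured against the face-to-face output. The change is worth making because it is cheap and bears on the decision WP3 is meant to inform; it does not invalidate the study.

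**What to change.** In the WP3 section on quantitative data analysis, keep kappa and add:
- the 2x2 table of clinic by home output;
- the proportion of clinic-high women who are high at home and of clinic-low women who are low at home, each with an exact 95% confidence interval;
- the paired difference in the proportion classed high risk, with its 95% confidence interval, and the exact McNemar test as support rather than as a pass/fail rule.

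In Table 2, have output 1 of the agreement study consider these alongside kappa and outcomes 3.1 to 3.3, and say that agreement is judged against the face-to-face output.

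The cost is one or two sentences and a few lines of analysis on data already to be linked. The drawback is that agreement among clinic-high women rests on about 18 women and will look less precise than kappa. The sample-size section should say so, for example with the 36% to 83% interval for 11 of 18.

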## Sample size

### WP1: Vfrac implementation within primary care

A sample size of six general practices has been chosen because discussions with primary care have identified three potential operational characteristics that may impact on uptake, ease of use and acceptability of Vfrac. These are IT system (EMIS Web and SystmOne), size (small versus large) and within different PCNs/clusters. The recruitment of six practices will enable us to observe and explore the various aspects of feasibility within and across these various characteristics.

